#### Questionnaire Return Process

A number of steps were taken to promote maximum return rates. If questionnaires were not returned within 14 days of distribution, parents were contacted by phone. During the call, the research assistant answered any questions about the questionnaires and arranged for another to be sent if required. A second reminder call was made if questionnaires were not returned within 21 days of distribution. If questionnaires were not received within 28 days of distribution parents were sent a reminder letter, and a second copy of the questionnaire mailed to them.

### Intervention

*The ABCD Parenting Young Adolescents Program *(Cann, Burke & Burke, 2003): ABCD is a group program for parents of children aged from 9-14 years. The program is a brief psycho-educational intervention based on social learning principles and incorporating acceptance-based strategies. An emphasis is placed on active skills building and problem solving, and strategies that have been shown by research to reduce distress in interpersonal relationships. The aim of the program is to provide parents with information and skills for developing and maintaining trusting, positive and accepting relationships with their young adolescents which, in turn, encourages them to test their independence within safe boundaries.

The program is delivered over six consecutive weeks. During each 2-hour session parents have the opportunity to discuss, practice and receive feedback on a range of strategies and ideas. The program content is designed to enhance parental understanding and skills for assisting their children to make the transition to adolescence. Content is organised under four themes: 1) developing understanding and empathy for adolescents; 2) building strong relationships; 3) building responsibility and autonomy; and 4) parental self-care. An overview of program objectives and content is provided in Table 1.

**Table 1 T1:** ABCD Parenting Young Adolescents Program Overview

Theme	Objective	Content
Developing understanding/empathy for adolescents	To provide participants with an understanding of the developmental and social challenges facing adolescents and their parents during the transition from childhood to adulthood. To increase parental empathy for their adolescent To assist parents to identify their core values relating to parenting and establish concrete actionable goals.	Understanding Adolescence (Session 1) Parenting Traps (Session 1) Identifying Family Values (Session 2)
Building strong relationships:	For participants to have a clear a clear understanding of the importance of establishing and maintaining a positive parent-adolescent relationship. For participants to practice a range of strategies for building and enhancing their skills for connecting and communicating with their adolescents.	Connecting (Session 2) Positive Feedback (Session 2) Communicating (Session 3)
Building adolescent responsibility and autonomy	For parents to be able to effectively use a model for establishing boundaries around their own and their adolescent's behaviour. To provide parents with skills for dealing with problems arising with their adolescent. To provide parents with strategies for backing up agreements and/or parent decisions. To assist parents to identify, prevent and/or manage potential risk-related problems facing their adolescent.	Boundaries (Session 4) Problem Solving (Session 4 & 5) Setting Limits (Session 5) Monitoring (Session 5) Problem Solving and Risk Taking (Session 6)
Parental Self-Care	For parents to develop a range of options for maintaining their own well-being. To provide parents with a range of information regarding seeking help.	Dealing with Strong Emotions (Session 5 & 6) Self Care (Session 6) Getting Support (Session 6)

#### Facilitator Training

Five group facilitators were trained by the first author, one of the program developers, thus a total of 6 facilitator's delivered programs as part of the project. The level of training was matched to the needs of the facilitator so that less experienced trainers received more comprehensive training in delivering group interventions, conducting parenting training, responding to group processes issues and content specific to the ABCD Parenting Program. Facilitators with more experience in delivering group based parenting interventions received training in the ABCD Parenting Program theory and content only. Prior to delivering groups independently, all facilitators co-facilitated groups with the first author until they demonstrated competence in delivery of the program. All facilitators received weekly supervision from the first author throughout the project. Audiovisual footage of group sessions was used throughout these supervision sessions to allow for the provision of feedback on both group process and program content.

#### Group Materials

The ABCD Parenting Program was delivered as prescribed in the ABCD Parenting Young Adolescent Facilitators Manual [74]. The manual contains detailed session notes for facilitators and PowerPoint slides and parent handouts for use during the program.

#### Treatment Adherence

Treatment fidelity and integrity was maintained across facilitators via the use of a manualised program [74]. Facilitators completed adherence checklists at the end of each group session. All group sessions were videotaped and segments of each session were randomly selected and reviewed in supervision sessions to ensure adherence to program content and process.

#### Statistical Power

As there were no meta-analyses exploring outcomes of adolescent parenting programs available at the time of the study, results of a meta-analysis exploring the effectiveness of behavioural parenting training in modifying antisocial behaviour in children was used for power analyses[75,76]. This paper demonstrated a medium to large effect size for child behaviour outcome measures (d = 0.84) and a small to medium effect size for parental adjustment outcome measures (d = .44) [77]. G-Power [78,79] was used to calculate the required sample size. This analysis indicated that for power = 0.80 with an alpha = 0.01, 21 participants per group would be required for child outcome variables, and 64 participants per group would be required for parental adjustment variables. Given the expected high rate of drop-outs and loss to follow-up for participants in the study, particularly those on the wait-list, the number of participants recruited to the experimental and wait-list groups was increased to 90, ensuring that the required sample size was achieved.

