## Results

### Recruitment

Participant recruitment commenced in January 2005 and was completed in February 2007, at which time 180 families had enrolled to participate, ensuring an adequate number of participants for statistical comparison. Recruitment drives were conducted at the commencement of each school term. The first ABCD Parenting Program group commenced in May 2005 and the final intervention group commenced in February 2007. Twenty-one ABCD Parenting Program groups were conducted throughout this period.

A total of 409 parents were contacted to complete an intake call. Twenty-one families (5%) were excluded from the study as they did not meet the eligibility criteria for one or more reasons. Of these, eight adolescents were receiving other specialist services, eight adolescents had a medical condition or physical disability, seven adolescents and four parents had a mental illness, four adolescents had learning or developmental difficulties, one was a non-custodial parent without regular access to their children, and one was non-English speaking. Thirteen (3%) parents chose not to continue with the intake call after receiving verbal information about the ABCD Parenting Program and the associated research.

Three hundred and seventy five eligible (92%) parents completed intake and were mailed a plain language statement, consent form and family demographic survey. The majority of intake calls were completed with the child's mother (79.9%), 42.1% of target children were female, and the age of target children ranged from 9 to 14 years (M = 11.81, SD = 1.41). One hundred and eighty parents returned their consent form and family demographic survey to register for the program.

One hundred and ninety-five (52%) parents who completed intake did not register for the program. Reasons for non-registration included; other family/life issues (36.1%), problem resolved (18.1%), verbal project explanation unclear (10.8%), written project information unclear (19.5%), not comfortable completing questionnaires (14.5%), didn't want to wait (13.3%), program not appropriate for needs (13.4%), can't remember (6.0%), and other (75.0%). Many families provided multiple reasons for non-registration.

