Parents that did not register for the program did not differ from those that did register in terms of their adolescent's age (*t*(353.9) = -1.23, *p *> .05) or sex (*χ*^2^(1) = .64, *p *> .05). Parents that registered for the program(*M *= 1039.6, *SD *= 68.1) had a higher Socioeconomic Indexes for Areas(SEIFA) Index of Relative Socio-economic Advantage and Disadvantage based on residential postcode(*t*(342.9) = 2.39, *p *= .017) than those who did not register for the program(*M *= 1021.5, *SD *= 74.6). This indicates that families of lower socioeconomic status were less likely to register for the program.

The 180 participants who returned consent forms and family demographic surveys were randomly allocated to intervention (n = 90) or wait-list control (n = 90) conditions. Of those allocated to the intervention condition 82 (91%) were successfully enrolled into a group. It was not possible to enrol 8 (9%) registered parents in the intervention condition into groups. Eight (10%) of the 82 enrolled in a group did not attend. Of the 90 parents allocated to the intervention condition 76 (84%) returned a completed pre-questionnaire. This included all 74 parents who attended a group and two parents who were enrolled in a group but did not attend. Sixty-eight (76%) of the 90 parents allocated to the wait-list condition returned a completed pre-questionnaire. This information is presented in Figure 1 below.

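### The stated 21 and 64 per group do not follow from the stated inputs for a between-arm comparison, so the claim of an adequate sample is unsupported for parental adjustment

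*Protocol article*

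**What the plan says.** The Statistical Power section of the protocol article takes two standardised effects from a meta-analysis. One is a "medium to large effect size for child behaviour outcome measures (d = 0.84"). The other, smaller effect is described as a "small to medium effect size for parental adjustment outcome measures (d = .44"). It then says that "G-Power [78,79] was used to calculate the required sample size", and gives the result for the larger effect: "This analysis indicated that for power = 0.80 with an alpha = 0.01, 21 participants per group would be required for child outcome variables". For the smaller effect the same sentence reports that "64 participants per group would be required for parental adjustment variables". It names neither the test nor its sidedness, and gives no covariate or correlation.

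To allow for drop-out, "the number of participants recruited to the experimental and wait-list groups was increased to 90, ensuring that the required sample size was achieved". The Recruitment part of the Results repeats the assurance for the 180 enrolled families: "ensuring an adequate number of participants for statistical comparison". It then reports 90 parents randomised to each arm. In the intervention arm 76 returned a pre-questionnaire; for the other arm, "Sixty-eight (76%) of the 90 parents allocated to the wait-list condition returned a completed pre-questionnaire".

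The Planned Statistical Analysis section assesses efficacy by comparing wait-list with intervention in 2 × 2 mixed MANCOVAs, with condition as the between-subjects factor and time (post, follow-up) as the within-subjects factor.

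**The concern.** The section prints both the inputs (d, alpha, power) and the outputs (n per group), so the calculation can be checked. For two independent arms, 21 and 64 are far too small at alpha 0.01. For parental adjustment the stated requirement is about half the two-sided one, and even the 90 per group recruited lies below it.

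What is at stake is how a null result is read. Study Design lists parental psychosocial wellbeing among the primary outcomes (the Abstract places it among the secondary ones), and the Planned Statistical Analysis section puts parental wellbeing in the primary analyses. A reader who accepts the two assurances would take a null finding there as coming from a comparison with at least 80% power. The article gives no basis for that.

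**Working it through.** **Inputs.** From Statistical Power: d = 0.84 and d = 0.44 (so SD = 1), alpha = 0.01, power = 0.80. From Recruitment: 90/90 randomised, 76/68 with a pre-questionnaire. Sidedness is not stated, so both are shown.

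**1. Attempt to reproduce 21 and 64 as a between-arm calculation.** Normal approximation: n per group = 2(z_alpha + z_power)² / d².

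- Two-sided: z sum = 2.576 + 0.842 = 3.417. For d = 0.84: 2 × 3.417² / 0.7056 = 33.1. For d = 0.44: 2 × 3.417² / 0.1936 = 120.7.
- One-sided: z sum = 2.326 + 0.842 = 3.168. For d = 0.84: 28.4. For d = 0.44: 103.7.

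The exact noncentral-t calculation adds one to three per group:

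| Test, alpha 0.01, power 0.80 | d = 0.84 | d = 0.44 |
|---|---|---|
| Stated in the article | 21 | 64 |
| Two independent arms, two-sided | 35 | 123 |
| Two independent arms, one-sided | 30 | 106 |
| One-sample or paired t, two-sided | 20 | 64 |

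The stated pair is not reproduced for two independent arms on either sidedness.

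**2. A possible origin.** The one-sample or paired t-test has noncentrality d√n on n − 1 degrees of freedom. At two-sided alpha 0.01 it needs 64 for d = 0.44 (power 80.3%; 63 gives 79.5%) and 20 for d = 0.84 (power 80.2%; 21 gives 82.9%). The stated figures match this to within one person. It tests within-person change, not arm against arm. That this is how the figures arose is an inference; the article does not say.

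**3. Power of an unadjusted between-arm t-test at alpha 0.01.** Noncentrality = d√(n1·n2/(n1+n2)). Example for d = 0.44 at 76/68: 0.44 × √(76 × 68 / 144) = 2.636, against a two-sided critical value of 2.611 on 142 degrees of freedom, which gives 51.2%.

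| n per arm | d = 0.44 two-sided | d = 0.44 one-sided | d = 0.84 two-sided |
|---|---|---|---|
| 64/64 | 45.2% | 55.4% | 98.3% |
| 76/68 | 51.2% | 61.2% | 99.2% |
| 90/90 | 63.6% | 72.7% | 99.9% |

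The smallest effect detectable with 80% power at 76/68, two-sided and unadjusted, is d = 0.58.

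**4. Effect of adjusting for the pre-score.** Assumption: the covariate is the pre-score, with correlation r to the outcome; r is not in the article. Residual variance is 1 − r², so d becomes 0.44/√(1 − r²). One time point, two-sided alpha 0.01, no further loss:

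| r | 76/68 | 90/90 |
|---|---|---|
| 0.3 | 56% | 69% |
| 0.5 | 67% | 79% |
| 0.6 | 75% | 86% |
| 0.7 | 86% | 94% |

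**5. The step from 64 to 90.** It tolerates a loss of (90 − 64)/90 = 28.9%. Against an unadjusted requirement of 123 (or 106 one-sided), 90 falls short even with no loss.

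**The case against.** The strongest objection is that step 3 describes a test the trial does not plan. The planned MANCOVAs carry covariates and use two time points, and both can raise power. This stands. A reader might infer from the unadjusted figures that the trial simply has 51% to 64% power for parental adjustment. The article does not support that flat statement: the range holds only for a two-sided, unadjusted test at one time point. With a pre-score correlation near 0.7, one time point would exceed 80% at 76/68. If post and follow-up were averaged as well, with all correlations equal to r, power at 76/68 would be about 82% to 96% for r from 0.3 to 0.7. But these are assumptions the article does not make, and all of them precede any loss after the pre-questionnaire. They show that the sample might suffice, not that the stated calculation shows it does.

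A reader might also infer that 21 and 64 contradict each other. They do not clearly do so, since one paired test at the stated alpha comes within one person of both. The fault is better described as a calculation that does not fit the between-arm question.

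Nor is the whole sample too small. For child outcomes the corrected 35 per group is well below both 76 and 68.

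Finally, an article condenses its protocol. That excuses omissions, but here inputs and results are both printed and do not agree.

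**Conclusion.** Wrong as written. The stated 21 and 64 per group do not follow from d = 0.84 and d = 0.44 at alpha 0.01 and 80% power for two independent arms, on either sidedness. For parental adjustment the unadjusted two-sided requirement is nearly double the printed one (123 against 64).

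The consequence is confined to parental adjustment. There, both assurances of an adequate sample are unsupported: without adjustment, power is below 80% even with all 90 per arm analysed, and any rescue depends on a correlation or a use of both time points that the article does not state. The true power of the planned analysis cannot be fixed from the article. For child outcomes the error has no practical effect on the number achieved.

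**What to change.** 1. In Statistical Power, replace 21 and 64 with the between-arm figures at the declared alpha of 0.01 (35 and 123 per group, two-sided, unadjusted), or state the test, sidedness and correlation that justify a smaller number.
2. Report the power, or the detectable effect, at the analysable number. Unadjusted and two-sided at alpha 0.01, the detectable effect at 76/68 is d = 0.58. If adjustment for the pre-score is relied on, give the assumed r and the resulting power.
3. Limit the two adequacy statements, in Statistical Power and in Recruitment, to child outcomes, unless the justification in item 1 covers parental adjustment.

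The declared alpha should stay as it is, since recruitment has closed. The cost is text only, with no extra participants. The downside is a less favourable stated power for parental adjustment.

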**Methods/Design:**

One hundred and eighty parents were randomly allocated to an intervention or wait list control group. Parents in the intervention group participated in the ABCD Parenting Young Adolescents Program, a 6-session behavioral family intervention program which also incorporates acceptance-based strategies. Participants in the Wait List control group did not receive the intervention during a six month waiting period. The study was designed to comply with recommendations of the CONSORT statement. The primary outcome measures were reduction in parent-adolescent conflict and improvements in parent-adolescent relationships. Secondary outcomes included improvements in parent psychosocial wellbeing, parenting self-efficacy and perceived effectiveness, parent-adolescent communication and adolescent behavior.

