## Method/Design

### Study Procedures

#### Study Design

This study was a randomised controlled trial in which 180 parents of adolescents were randomly allocated to one of two conditions; intervention or a wait-list control group. Parents in the intervention group participated in the ABCD Parenting Young Adolescents Program, a 6-session behavioral family intervention program which also incorporates acceptance-based strategies [57,59,60]. Those in the wait-list control group did not receive intervention during the 6-month wait list period. Assessments were conducted prior to intervention, immediately after intervention, and 6 months and 18 months after completion of intervention. The wait-list control group completed assessments at the same time as pre, post and 6-month follow-up assessments. The primary outcome measures were improvements in parental psychosocial well being, parenting practices and parent-adolescent relationships. Secondary outcomes included improvements in adolescent behavior and perceived parenting competence. The study was designed to be compliant with the recommendations of the CONSORT statement. [61,62]

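### The statement that the required sample size was achieved has no stated basis for parent-adolescent relationships, the only outcome that is primary in both outcome statements

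*Protocol article*

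**What the plan says.** The article names its primary outcomes twice, and the two lists differ.

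- **Abstract, Methods/Design:** "The primary outcome measures were reduction in parent-adolescent conflict and improvements in parent-adolescent relationships". The same paragraph adds: "Secondary outcomes included improvements in parent psychosocial wellbeing, parenting self-efficacy and perceived effectiveness, parent-adolescent communication and adolescent behavior".
- **Study Design:** "The primary outcome measures were improvements in parental psychosocial well being, parenting practices and parent-adolescent relationships". It adds: "Secondary outcomes included improvements in adolescent behavior and perceived parenting competence".

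Planned Statistical Analysis then describes the primary analyses as covering four domains: parental wellbeing, parenting practices, relationships and adolescent behaviour. The primary aim at the end of the Background lists the same four.

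Statistical Power borrows two effect sizes from a meta-analysis of behavioural parent training for child antisocial behaviour: d = 0.84 for child behaviour and d = .44 for parental adjustment. With power 0.80 and alpha 0.01 it concludes that "21 participants per group would be required for child outcome variables, and 64 participants per group would be required for parental adjustment variables". Recruitment was raised to 90 per group to allow for drop-out, "ensuring that the required sample size was achieved". Results, Recruitment repeats the conclusion for the 180 enrolled families: "ensuring an adequate number of participants for statistical comparison".

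**The concern.** The calculation and the conclusion do not have the same scope. The calculation covers two classes of outcome; the adequacy statements carry no limit. Between them lie relationships (primary in both lists), conflict (primary in the Abstract) and parenting practices (primary in Study Design), none of which has an effect size or a required number. On the Abstract's list, no primary outcome was sized at all.

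At stake is how the result can be interpreted. A reader who meets a null finding on relationships or conflict would have a published statement that the sample was sufficient, but no derivation behind it for that outcome.

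**Working it through.** **Which outcomes were sized**

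| Outcome | Abstract | Study Design | Effect size and number per group |
|---|---|---|---|
| Parent-adolescent relationships | primary | primary | none |
| Parent-adolescent conflict | primary | not listed | none |
| Parenting practices | not listed | primary | none |
| Parental wellbeing | secondary | primary | d = .44, 64 (as parental adjustment) |
| Adolescent behaviour | secondary | secondary | d = 0.84, 21 |

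**Reproducing the plan's own figures**

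Inputs from Statistical Power: power 0.80, alpha 0.01, d = 0.84 and .44, equal groups. Sidedness is not stated. The normal approximation is n per group = 2(z_alpha + z_power)² / d².

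- Two-sided: (2.576 + 0.842)² = 11.68. For d = 0.84, 23.36 / 0.7056 = 33.1, so 34. For d = .44, 23.36 / 0.1936 = 120.6, so 121. The exact t-test gives 35 and 123.
- One-sided: (2.326 + 0.842)² = 10.04. This gives 29 and 104, or 30 and 106 by the t-test.

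So 21 and 64 do not follow from the stated terms. The nearest simple match is one-sided alpha 0.05, with 18 and 64 (19 and 65 by the t-test), which contradicts the stated alpha. Adjustment for a covariate with an assumed correlation of 0.7 gives about 18 and 62 at two-sided alpha 0.01, but Statistical Power mentions no covariate or correlation.

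**If relationships belong to the parental class (d = .44)**

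With 90 per arm the noncentrality is 0.44 × √(90/2) = 2.95. Power at alpha 0.01 by the t-test is 64% two-sided and 73% one-sided. With the 76 and 68 who returned pre-questionnaires (Results) it is 51% and 61%.

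**Detectable effect at 80% power, two-sided alpha 0.01, unadjusted**

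Approximately d = 3.417 × √(1/n1 + 1/n2); exact t-test values follow.

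- 90 and 90: 3.417 × 0.1491 = 0.509; exact 0.514.
- 76 and 68: 3.417 × 0.1669 = 0.570; exact 0.577.
- 64 and 64: exact 0.612.

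**With adjustment for the pre score**

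Multiply by √(1 − r²). The documents give no r, so it is an assumption.

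| Assumed r | Factor | 90 and 90 | 76 and 68 |
|---|---|---|---|
| 0.3 | 0.954 | 0.49 | 0.55 |
| 0.5 | 0.866 | 0.45 | 0.50 |
| 0.6 | 0.800 | 0.41 | 0.46 |
| 0.7 | 0.714 | 0.37 | 0.41 |

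**Dependence on the unknown effect**

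For 90 per arm, unadjusted, two-sided alpha 0.01, power is 28% at d = 0.3, 53% at 0.4, 77% at 0.5 and 92% at 0.6. All four effects are assumed.

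**The case against.** Several counter-arguments have force.

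1. **The sized classes are not outside the efficacy question.** Parental wellbeing is primary in Study Design, and Planned Statistical Analysis puts both sized classes in the primary analyses. A reader might infer that the adequacy claim concerns only outcomes that do not decide efficacy; the documents do not support that. What stands is narrower: relationships, conflict and parenting practices were not sized.
2. **The proxy is disclosed.** Statistical Power says no meta-analysis of adolescent programs was available. That explains borrowing class-level effects, but not an unlimited adequacy conclusion.
3. **Relationships may have been meant as parental adjustment.** The parental stress measure (SIPA) has an adolescent-parent relationship domain, and the larger figure, 64, would govern whichever class applied. This is plausible, but the article never makes the link, and both outcome lists name relationships separately from parental wellbeing. Granting it gives 64% power with 90 per arm on the stated terms.
4. **The planned analysis is a Mancova over post and follow-up, not a t-test.** This is the strongest point. With r = 0.6 the detectable effect at 90 per arm is about 0.41, below .44. If the two post-intervention times are also averaged, with an assumed correlation of 0.7 between them and equal effects at both, the factor is √(0.85 − 0.36) = 0.70, giving about 0.36 with 90 per arm and 0.40 with 76 and 68. The design may therefore be adequate for an effect of that size, but only under correlations that the power section does not state.
5. **Recruitment is closed.** Only the wording can change, which limits the remedy but does not remove the need for it.

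**Conclusion.** The point holds as one about an unsupported statement. The required numbers cover child behaviour and parental adjustment only. For relationships, conflict and parenting practices the claims in Statistical Power and in Results, Recruitment have no stated basis.

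A reader might go further and infer that the trial is too small for relationships. The documents do not support that, because they give no effect size for this outcome and the power figures at d = 0.3 to 0.6 only illustrate a range. What can be said is conditional: at d = .44, 90 per arm gives about 64% power two-sided or 73% one-sided. That figure assumes alpha 0.01, a plain two-group comparison at one time and all 90 per arm analysed. Covariate adjustment could bring it above 80% if the correlation is high enough.

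**What to change.** 1. Reconcile the primary outcomes across the Abstract, Study Design and Planned Statistical Analysis. Until that is done, nobody can say which outcome the sample size should serve.
2. Do not carry 21 and 64 forward unless the test, the sidedness and any covariate correlation that produce them are stated.
3. Replace both adequacy claims (Statistical Power; Results, Recruitment) with the effect detectable on the reconciled primary outcome at 80% power and two-sided alpha 0.01: about d = 0.51 with 90 per arm and 0.58 with 76 and 68, unadjusted. Add the figure for the planned covariate-adjusted analysis with its assumed correlation stated, for example about 0.41 and 0.46 if r = 0.6.
4. Say plainly that no separate number was derived for relationships, conflict or parenting practices.

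The cost is a few sentences and a recalculation with the software already used, with no extra participants. The downside is that the stated adequacy becomes less favourable.

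### For the parental-adjustment outcomes, the article's flow figures do not support its statements that 90 per arm, or 180 enrolled, ensured an adequate sample

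*Protocol article*

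**What the plan says.** All references are to the protocol article.

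- **Statistical Power** gives two requirements, both "for power = 0.80 with an alpha = 0.01": "21 participants per group would be required for child outcome variables" (effect size 0.84), and "64 participants per group would be required for parental adjustment variables" (effect size 0.44). It expects substantial drop-out, above all on the wait-list, but states no rate. For that reason, it says, the number per arm "was increased to 90, ensuring that the required sample size was achieved".
- **Recruitment** (under Results) dates the close of recruitment to February 2007, "at which time 180 families had enrolled to participate, ensuring an adequate number of participants for statistical comparison".
- The same section then reports the flow. "Sixty-eight (76%) of the 90 parents allocated to the wait-list condition returned a completed pre-questionnaire"; in the intervention arm it was 76 of 90 (84%).
- **Planned Statistical Analysis** bases the efficacy comparison on the post-intervention and follow-up assessments, with condition as the between-subjects factor. Both completer and intention-to-treat analyses are planned.
- **Assessment Schedule** shows that wait-list parents received all their questionnaires by mail, for postal return.

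**The concern.** The article promises that the required number was secured and then prints flow figures that leave very little of the allowance behind that promise. The first mailed form already had 24.4% non-return on the wait-list (22/90), and the two assessments that carry the efficacy comparison come after it. The Recruitment sentence is the weaker of the two assurances, because it judges adequacy from families enrolled, not from parents with outcome data.

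The requirement at issue is the one for parental adjustment. Study Design lists parental psychosocial wellbeing as a primary outcome (the Abstract places it among the secondary ones), and Planned Statistical Analysis puts parental wellbeing in the primary analyses. If the assurances stand, a null result on these outcomes could be read as coming from a trial of secured size.

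**Working it through.** **Inputs.** Required per group 64 (parental adjustment) and 21 (child); recruited 90 per arm; d = 0.44 and 0.84; power 0.80; alpha 0.01, sidedness not stated (all Statistical Power). Pre-questionnaires returned: 68 wait-list, 76 intervention (Recruitment). Loss after pre is not given, so 10%, 20% and 30% are assumptions.

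**1. The plan's own 64.** Normal approximation for two means: n per group = 2(z_alpha + z_power)²/d², with z_power = 0.8416 and d² = 0.1936.

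- Two-sided alpha 0.01: 2(2.5758 + 0.8416)²/0.1936 = 120.7, so 121. The exact t calculation gives 122.32, so 123.
- One-sided alpha 0.01: 2(2.3263 + 0.8416)²/0.1936 = 103.7, so 104. The exact t calculation gives 105.04.
- One-sided alpha 0.05: 2(1.6449 + 0.8416)²/0.1936 = 63.9, so 64. The exact t calculation gives 64.56.
- Two-sided alpha 0.05: 82 (normal), 82.05 (t).

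So 64 is not reproduced at the stated alpha. It is matched only by a one-sided alpha of 0.05, which the article does not state. The 21 is not reproduced at alpha 0.01 either (34 to 35 two-sided, 29 to 30 one-sided).

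**2. The allowance, taking 64 as the plan does.**

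- Allowance per arm: 90 − 64 = 26 (26/90 = 28.9%).
- Wait-list without pre-intervention data: 90 − 68 = 22, and 22/26 = 84.6% of the allowance. Remaining: 68 − 64 = 4, and 4/68 = 5.9%.
- Intervention without pre-intervention data: 90 − 76 = 14, and 14/26 = 53.8%. Remaining: 76 − 64 = 12, and 12/76 = 15.8%.
- Crediting the larger arm through the harmonic mean: 2 × 76 × 68/144 = 71.8 per arm. The equivalent of 64 per arm is lost once later loss in both arms exceeds 1 − 64/71.8 = 10.8%.

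**3. Analysable numbers and power for d = 0.44** (two-sample t; equal later loss in both arms, counted from those who returned the pre-form):

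| Later loss (assumed) | Wait-list | Intervention | Power, two-sided alpha 0.01 | Power, one-sided alpha 0.05 |
|---|---|---|---|---|
| 0% | 68 | 76 | 0.51 | 0.84 |
| 10% | 61.2 | 68.4 | 0.46 | 0.80 |
| 20% | 54.4 | 60.8 | 0.40 | 0.76 |
| 30% | 47.6 | 53.2 | 0.34 | 0.71 |

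With all 90 per arm and no loss, power at two-sided alpha 0.01 is 0.64.

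**4. Child outcomes.** The allowance is 90 − 21 = 69, and 22/69 = 32% of it is used. Even 48 wait-list parents exceed both the stated 21 and the 35 that a two-sided alpha of 0.01 would require.

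**The case against.** **No shortfall is shown.** A reader might infer that the trial had already fallen below its target. It had not: both arms exceed 64 at pre, the only time point reported, and all later loss above is assumed. This stands, and limits the point to an unsupported assurance.

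**Non-return is not withdrawal.** One might infer that 22 wait-list parents were lost. The article reports only that one form was not returned. The efficacy factor is post and follow-up, an intention-to-treat analysis is planned, and these parents could still supply later data. This stands in part. They have no pre-intervention scores, which the maintenance comparison across pre, post and follow-up uses. A complete-case analysis adjusting for those scores would also drop them, though the article does not name its covariates.

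**Statistical Power does separate required from recruited numbers.** It gives drop-out as the reason for going from 64 to 90, so it cannot be said to treat enrolment as analysable data. That criticism fits only the Recruitment sentence.

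**The allowance argument depends on 64.** A reader might take it to hold whatever the target is. It does not: 26, 4 and 5.9% are all distances from 64. At about 105 to 123 per group, 90 per arm contained no allowance at all. This stands. It changes how the point must be expressed, but makes the assurances less tenable.

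**Modest loss costs little power.** True on the one-sided 0.05 reading: 0.80 at 10% later loss and 0.76 at 20%. The article states alpha 0.01, where power is already 0.51 with 76 and 68.

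**The flow is printed openly.** It follows in the same Results section, and Strengths and Limitations promises a thorough account of attrition. That lowers the risk of misreading but does not make the assurances correct.

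**Conclusion.** The point holds for the parental-adjustment outcomes only. Against the plan's own 64, the wait-list arm had used 22 of its 26 allowed losses by return of the pre-questionnaire. It can miss at most 4 of the remaining 68 (5.9%) at post and 6-month follow-up, unless early non-returners supply later data. Nothing in the article supports so low a rate, and its Statistical Power section expects high drop-out in that arm.

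The 64 cannot itself serve as proof of adequacy. On the stated inputs the need is about 105 to 123 per group, more than were randomised to either arm.

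The power figures assume a simple two-group comparison, as the quoted effect sizes and per-group numbers imply. Covariate adjustment could raise them, but the article gives no correlation from which to say by how much. The documents do not establish an actual shortfall against 64, and the 21 per group for child outcomes remains comfortably attainable.

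**What to change.** - In Statistical Power and in Recruitment, replace both assurances with the numbers the flow gives: 76 intervention and 68 wait-list parents with pre-intervention data.
- Limit the statement to parental-adjustment outcomes.
- Give the analysable numbers under later loss of 10%, 20% and 30%, labelled as assumptions (wait-list about 61, 54 and 48; intervention about 68, 61 and 53), and say whether parents without a pre-form can contribute later data.
- Judge adequacy by parents with outcome data at post and 6 months, not by the 180 enrolled.
- Do not carry 64 forward as a benchmark. State the sidedness and report the power available for d = 0.44: at two-sided alpha 0.01, 0.64 with 90 per arm and 0.51 with 76 and 68.

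The cost is wording only, with no extra enrolment. The stated adequacy becomes less favourable.
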